## Abstract

**Background:**

Continuously high rates of overdose deaths in Sweden led to the decision by the Skåne County to initiate the first regional take-home naloxone program in Sweden. The project aims to study the effect of overdose prevention education and naloxone distribution on overdose mortality in Skåne County. Secondary outcome measures include non-fatal overdoses and overdose-related harm in the general population, as well as cohort-specific effects in study participants regarding overdoses, mortality and retention in naloxone program.

**Methods:**

Implementation of a multi-site train-the-trainer cascade model was launched in June 2018. Twenty four facilities, including opioid substitution treatment units, needle exchange programs and in-patient addiction units were included for the first line of start-up, aspiring to reach a majority of individuals at-risk within the first 6 months. Serving as self-sufficient naloxone hubs, these units provide training, naloxone distribution and study recruitment. During 3 years, questionnaires are obtained from initial training, follow up, every sixth month, and upon refill. Estimated sample size is 2000 subjects. Naloxone distribution rates are reported, by each unit, every 6 months. Medical diagnoses, toxicological raw data and data on mortality and cause of death will be collected from national and regional registers, both for included naloxone recipients and for the general population. Data on vital status and treatment needs will be collected from registers of emergency and prehospital care.

**Discussion:**

Despite a growing body of literature on naloxone distribution, studies on population effect on mortality are scarce. Most previous studies and reports have been uncontrolled, thus not being able to link naloxone distribution to survival, in relation to a comparison period. As Swedish registers present the opportunity to monitor individuals and entire populations over time, conditions for conducting systematic follow-ups in the Swedish population are good, serving the opportunity to study the impact of large scale overdose prevention education and naloxone distribution and thus fill the knowledge gap.

**Trial registration:**

Naloxone Treatment in Skåne County - Effect on Drug-related Mortality and Overdose-related Complications, NCT 03570099, registered on 26 June 2018.

## Background

In individuals with opioid use disorder or misuse of opioids, opioid-related overdose is the worldwide leading cause of premature deaths. Compared to the general population, people using opioids in Europe are between five and ten times more likely to die than their peers of the same age and gender [1]. Northern Europe and Scandinavia are greatly affected by high rates of opioid-related overdose deaths, and Sweden has experienced a steady increase during the last decade accounting for the second highest rates in Europe [2, 3]. Opioid overdoses are, to a large extent, preventable as a significant part (50–96%) of heroin users reported witnessing at least one clinically well-defined overdose [4], leaving a window of opportunity to intervene. Brief overdose training has been shown to be sufficient [5] and bystanders are willing and able to engage in life saving action [6, 7]. Having no addictive or psychoactive effect, the opioid antagonist naloxone has no abuse potential, is safe and effective, if given soon enough after the occurrence of an opioid overdose. Naloxone reverses the negative effect of opioids on respiratory depression and decreased consciousness. Serious adverse effects are rare [8, 9]. In 2014, the World health organization recommended that naloxone should be made available for all individuals likely to witness an opioid overdose [10]. Over the past two decades, there has been an expansion of overdose prevention education and naloxone distribution (OPEND) programs training bystanders how to intervene during a witnessed opioid overdose. Studies have shown that take-home naloxone (THN), accompanied with education and training related to overdose management, may be associated with decreased overdose related mortality [9, 11] and has been described to be cost-efficient [12, 13]. The evidence is insufficient as the majority of previous studies have been observational, uncontrolled studies, based on the self-report of administered naloxone doses and the outcome of overdose victims. Also, a recent randomized controlled trial in the US setting did not demonstrate an effect on overdose events from naloxone distribution, in comparison to an education-only study arm. This study, however, was limited in size and used any overdose event (non-fatal) as outcome, but demonstrates the complexity of overdose interventions and the large need for more controlled intervention studies in the area [14]. Thus, there is need for large scaled controlled studies, measuring the impact of THN programs on opioid overdose death in the population, as these studies have been scarce. Reports from Norway showed that implementation of a large scale governmental THN program was feasible, successfully distributing a high-volume of naloxone by the use of an already existing network of facilities [15, 16]. Research in United States by Walley et al. demonstrated a significant decrease in opioid related deaths in communities providing OPEND, where the greatest impact was observed in communities distributing > 100 THN kits per 100,000 inhabitants [17].

In June 2018, Skåne County was the first region of Sweden to launch a multi-site OPEND program in Sweden, aiming to study the impact of naloxone prevention education and distribution on overdose mortality and overdose-related morbidity within the population. This protocol describes the implementation for monitoring the effects such a program.

### Risk factors for overdoses

Recent non-fatal overdose has been shown to represent a marker for increased risk of subsequent fatal overdose [18–20]. Recent period of abstinence, such as post-release from prison [21–24] or inpatient treatment [25–27], polydrug use [28–32], are risk factors highly associated with opioid overdose. Retention in opioid substitution treatment (OST) is associated with reduction of mortality and morbidity [33–39]. However, the OST population in Europe is ageing, with a mean age of death (39.4 years) increasing steadily [1], and carries a high degree of burden when it comes to chronic disease and multi-morbidity [29, 40] which also adds to the risks of overdose. Contrary to many beliefs, tolerant older users have been shown to have a higher risk of death due to overdose than novice users [28, 41].

### Opioid overdose

Defined as loss in consciousness and respiratory depression, opioid overdose is not a rare event among people who use opioids. Reports from Norway and Sweden have shown that the majority (> 70%) of heroin users have experienced at least one previous non-fatal overdose [16, 42, 43]. Estimations show that approximately one in 20 to one in 30 opioid overdoses leads to death [36]. Research describes an array of direct and indirect negative consequences of non-fatal opioid overdoses, such as pulmonary [44, 45] and cardiovascular complications [46], peripheral neuropathy [47], cognitive impairment [48] and rhabdomyolysis, which can lead to muscular problems, kidney injuries or failure [49]. Indirect injuries, such as injuries caused by falling, burns and assault, during loss of consciousness, are also rather frequently displayed [47].

As non-fatal overdoses are far more common than fatal opioid overdoses it is difficult to estimate the impact even of larger naloxone distribution programs. As non-fatal overdose commonly leads to both internal and external injuries it is important to focus both on reduction in mortality and reduction in morbidity. It is, however, impossible to predict whether a reversed opioid overdose would have been fatal, had naloxone not been administered, nor if potential injuries would have been avoided. This, the addition of societal factors that fluctuate over time, such as availability of drugs and potency of opioids, makes the estimated impact of OPEND on mortality and morbidity problematic. As research has shown that survival time exceeded 20–30 min in a majority of opioid related overdose fatalities, there is an opportunity for intervention [50]. By using naloxone, opioid overdoses can efficiently and safely be reversed by witnessing bystanders [51, 52].

### Routes of naloxone administration

Opioid receptor antagonist naloxone has been used in emergency and hospital settings since the United States Food & Drug Administration (FDA) approval in 1971, for intravenous, intramuscular and subcutaneous administration [53]. Subsequently, intranasal administration was suggested as a safe and efficient alternative to the use of needles. Injectable naloxone has been used off-label for intranasal administration throughout several years by prehospital staff [54–60], emergency medical services [61] and in the emergency department [62] with satisfactory clinical effect, compared to IV or IM administration [59, 60, 63]. Approved by the FDA in November 2015 [63], pharmacokinetic studies comparing the new intranasal to intra muscular administration, have shown satisfying results [64–67].

### Education and training

Bystanders are willing and able to respond appropriately to an overdose situation [6, 7, 68]. Naloxone training significantly improves knowledge regarding prevention and correctly managing opioid related overdoses [69–73]. Researchers also have suggested other benefits of naloxone and CPR training; Seal and co-workers, in a small study following patients during 6 months after CPR training and naloxone distribution, demonstrated that past-30-day heroin injecting decreased in the study participants [74]. Also, from qualitative interviews with clients trained in overdose intervention and naloxone administration, Wagner and co-workers described feelings of increased empowerment in the participants [75].

### Opioid overdose mortality in Sweden

Reported incidence of drug related death is approximately four times higher in Sweden (92 deaths/million) [3] compared to the average of Europe (22.6 deaths/million) [1]. Acute onset lethal intoxications have gradually increased since 1991, accompanied by an increase of deaths involving other opioids such as buprenorphine, fentanyl, methadone and tramadol [1, 76]. Toxicology records show that opioids are present in 95% of the drug related deaths. These records also show a high, and increasing, proportion of cases exhibiting the presence of more than one substance, indicating that poly-drug use, to a large extent, contributed to their death. The slight decrease in numbers of drug related deaths between 2015 and 2016 unfortunately proved to be a short break in the otherwise increasing numbers [1–3], showing that these numbers do fluctuate over time, adding to the challenging task of drawing conclusions from the result of interventions.

### Naloxone availability in Sweden

The National Board of Health and Welfare’s review of the legal situation established, in June 2017, that naloxone could be prescribed to people at risk of overdose, in relation to current legislation [77]. Prior to this, naloxone prescription was not legal in Sweden [78]. In the region studied here, the present study started soon after naloxone prescription was made legal. Prior to the study, distribution of naloxone in the region is likely to have been virtually non-existent. Naloxone distribution was already carried out in the capital area of Denmark [79], in close connection to the southernmost regions of Sweden, and few months before the start of the present project, distribution was initiated in the Stockholm region. Also, earlier than that, unauthorized distribution from peer support groups has been reported from the Stockholm area. Although a limited amount of naloxone potentially may have reached the region across the nation border or from a geographical distance from the Stockholm area, availability of naloxone in the present target region is likely to have been very low prior to study start.

Before approval of the new high concentration nasal spray containing 1.8 mg of naloxone hydrochloride for the use by laypersons, the prefilled vial with a solution of 0.4 mg/ml was approved and available to order from April 2018. The nasal spray was available in June 2018 for the Swedish market.

Naloxone is to be prescribed directly to the patient, given that the patient has received information about how to recognize an opioid overdose, how to administer naloxone and how to give life support while waiting for ambulance to arrive [77]. While relatives or friends of the patient can receive information and education as above, naloxone can only be prescribed to the patient at risk [77]. As a way to make THN more available, changes in the regulations, made in November 2018, allowed registered nurses, not only physicians, to prescribe naloxone [77]. In the beginning of 2019, The National Board of Health and Welfare strongly recommended regional health care facilities to offer THN to all individuals at risk of opioid overdose. Although prescription of naloxone is restricted, the accompanying information, on how to act and administer naloxone in case of an overdose, is general and addresses both individuals with substance use and individuals at risk of becoming a bystander in an overdose situation [80]. There are no legal constraints for non-users of opioids, such as family members or other potential bystanders, to use naloxone to reverse overdoses.

## Methods/design

### Setting

The present setting is the county of Skåne, the southernmost county of Sweden with around 1.3 million inhabitants. The major city of the region is the city of Malmö, with around 315,000 inhabitants, and three other major cities (Helsingborg, Lund, and Kristianstad) with populations of 145,000 to 85,000 inhabitants. By Swedish measures, the region of Skåne has unique access to both needle exchange programs (NEP) and opioid substitution treatment (OST) clinics through a network of units which enable reaching a large proportion of illicit drug users at risk of an opioid overdose. The Skåne region has seen a considerable expansion of OST in recent years, and in November 2017, a total of 1514 patients were enrolled in OST in the region. The region has four NEPs, in the four largest cities of the region, and which are open on weekdays and administered by the departments of infectious diseases within the regular hospital system. Altogether, the NEPs of the region have around 1000 to 1100 patients enrolled annually. The number of people at risk of an opioid overdose in the region is likely difficult to establish, as overdoses may occur both to patients known in addiction treatment or harm reduction, based on their opioid dependence, but also to unregular opioid users including patients seen in treatment for other addictive disorders and who may occasionally misuse opioids.

Overdoses in the present region have been examined in several papers during the past decade. For example, it was documented in qualitative interviews that despite an overall willingness from heroin users to help peers who overdose, several potential barriers against adequate interventions by bystanders were identified, such as uncertainty about the victim’s own intentions, the influence of one’s own intoxication, and fear of police when calling the ambulance [81]. Also, a smaller survey carried out in OST patients in the same region demonstrated high prevalence of overdoses, but also a very high interest in participating in a potential naloxone program [78].

### The Skåne naloxone project

In accordance with the decision of the Health Board in Skåne County in December 2014, the Director of Health was commissioned to monitor the possibilities of conducting a pilot study on THN with intranasal naloxone, and to report the case in March 2015. Skåne County has since followed the development of ongoing clinical studies and ongoing projects. In March 2015, The Director of Health was commissioned to start an experimental project as soon as possible in the form of a clinical study using intranasal naloxone spray. The pilot project was started after naloxone distribution was made legal by the authorities and after the nasal spray became available, and it is to be run for 3 years and during this time frame the scope of the study could be expanded if additional evidence was to be added [82].

Since prescription or distribution to a third party is prohibited by law, a well-structured and efficient multi-site implementation and distribution should provide the means to reach a large proportion of high-risk individuals with a relatively high likelihood of becoming bystanders at overdose situations. Implementation of this type of intervention setting where bystanders will administer naloxone and use life-supportive interventions as taught by the naloxone providers is believed to be feasible in a Swedish setting. The project was launched in the second quarter of 2018 [83]. The project is conducted by a steering group with representation from the organization of the county (Region Skåne) as well as the director of the clinical trials support organization of the region, as well as the principal investigator (the last author of the present paper), and the project leaders (the remaining authors of the paper). The current naloxone distribution program will continue for 3 years, and study outcomes will be followed for up to 5 years.

#### Study aims

The present study is a prospective cohort study testing the effect of an intervention, and comparing the effect in comparison to a historic comparison period. The primary aim is to study whether the project has an effect on overdose mortality in the general population in the region. Secondary outcome measures include the effect on incidence of non-fatal overdoses and ambulance-witnessed outcome measures of non-fatal overdoses in the general population, as well as outcomes specific to the included cohort participants receiving naloxone prescriptions, including their program retention, mortality and non-fatal overdose morbidity.

#### Methods

All NEPs (4, in the cities of Malmö, Lund, Helsingborg and Kristianstad) and OST clinics (18, in the cities of Malmö, Lund, Helsingborg, Kristianstad, Ystad, Ängelholm, Landskrona and Trelleborg) in the region were included in the project and in the research study, conducted by Lund University. Attempting to reach the population of individuals who have chosen not to visit NEP or enrol in OST, the project also included the emergency ward and the opioid detox ward at Malmö Addiction Centre, serving a majority of the population in Skåne. The goal is to offer OPEND to all individuals visiting targeted units, and to include 2000 individuals in the study. In the present setting, as from hospital records, NEP participants can be identified from their unique personal identification numbers, as NEP participation and interventions by NEP staff are documented. This enables systematic and longitudinal research including NEP patients in the present setting, including follow-up of NEP attendance over time. Several previous research studies from the present setting have originating from the identification of patients attending NEP units in the region [42, 84–86].

#### Primary outcome measures

Mortality due to opioid intoxication in the general population in Skåne County in 2019–2023, compared with historical mortality due to opioid intoxication during 2013–2017. Number of deaths will be collected from national registries.

#### Secondary outcome measures

##### Secondary outcome measures in the general population

Reaction level of ambulance-attended opioid overdose survivors in the general population. Assessment of responsiveness in acute brain disorders using Reaction Level Scale (RLS-85) in ambulance. The RLS scale is graded from 1 (awake, no delayed reaction, oriented) to grade 8 (unconscious, no movements to painful stimuli) [Time Frame: 2019–2023].Respiratory rate of ambulance-attended opioid overdose survivors in the general population. Respiratory rate (breaths per minute) registered in ambulance [Time Frame: 2019–2023].Heart rate of ambulance-attended opioid overdose survivors in the general population. Heart rate (beats per minute) of opioid overdose survivors registered in ambulance [Time Frame: 2019–2023].Naloxone or other antidote administered by ambulance staff to ambulance-attended opioid overdose survivors in the general population [Time Frame: 2019–2023].Need of ambulance transport to hospital of ambulance-attended opioid overdose survivors in the general population, information registered in ambulance [Time Frame: 2019–2023].Incidence of opioid overdoses attended by ambulance or emergency hospital care (i.e. including non-fatal overdose cases), information registered in ambulance or from diagnostic codes registered in emergency hospital departments [Time Frame: 2019–2023].

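### Five of the six general-population secondary outcomes are defined only among ambulance-attended survivors, a group the programme can itself reshape, so their before/after contrasts carry a bias of unknown direction

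*Protocol article*

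**What the plan says.** The section on secondary outcome measures in the general population lists six outcomes. Five carry the same double restriction, survived and attended by ambulance:

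- "Reaction level of ambulance-attended opioid overdose survivors in the general population" (RLS-85)
- "Respiratory rate of ambulance-attended opioid overdose survivors in the general population"
- "Heart rate of ambulance-attended opioid overdose survivors in the general population"
- "Naloxone or other antidote administered by ambulance staff to ambulance-attended opioid overdose survivors in the general population"
- "Need of ambulance transport to hospital of ambulance-attended opioid overdose survivors in the general population"

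The sixth, incidence of overdoses seen by ambulance or emergency hospital care, is not limited to survivors but is still limited to attended cases.

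These are meant as effect measures. Study aims names the effect on "ambulance-witnessed outcome measures of non-fatal overdoses in the general population" among the secondary outcomes. Statistical methods sets 2013–2017 against 2019–2023 for general-population analyses. Measures adds that ambulance data can enter the comparison period only from early 2017, when the electronic system began.

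**The concern.** Both conditions for entering the group come after the intervention and can be changed by it.

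- **Survival.** The Discussion hypothesises fewer opioid deaths. An averted death that is attended joins the survivor group only because of the programme.
- **Attendance.** The training described under the cascade model teaches participants to call an ambulance and to give naloxone, so calling may rise. Setting also records "fear of police when calling the ambulance" as a barrier in this region, so a successful reversal may end without a call.

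Survivors attended before and after launch may therefore be differently selected. A change in mean RLS-85, or in the share given antidote or transported, could then reflect who was attended and not how severe overdoses had become. Neither a favourable nor an unfavourable result on these five outcomes could be read as a programme effect.

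**Working it through.** The article gives no planning figure for these outcomes (power was calculated for the primary outcome only), so there is nothing to reproduce. The check is a case-mix calculation.

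**Inputs.** Fatality f = 4%, inside the 1/20 to 1/30 given under Opioid overdose. Assumptions: half of survivors severe on arrival (s = 0.5); bystander naloxone reverses r = 10% of overdoses, equally across would-be deaths, severe and mild cases; every unreversed survivor is attended; a fraction c of reversed cases is called in, and these arrive mild.

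**Before, per 1000 overdoses.** Deaths 40; survivors 960, of whom 480 are severe. Severe share 480/960 = 50.0%. Severe or fatal: 480 + 40 = 520.

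**After.** Deaths 40 × 0.9 = 36; severe 480 × 0.9 = 432; unreversed mild 432; reversed 100. Attended survivors = 864 + 100c. Severe or fatal = 432 + 36 = 468, and 468/520 − 1 = −10%.

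| Case | Severe / attended survivors | Share | Severe or fatal |
|---|---|---|---|
| Before | 480/960 | 50.0% | 520 |
| All reversed cases called in | 432/964 | 44.8% | 468 |
| Half called in | 432/914 | 47.3% | 468 |
| None called in | 432/864 | 50.0% | 468 |

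**Averted deaths arriving severe.** Suppose a quarter of the 40 would-be deaths (10) also survive to arrive severe. Deaths become 26 and severe survivors 442, so severe or fatal stays at 468. The share is 442/974 = 45.4% if all reversed cases are called in, 442/924 = 47.8% if half are, and 442/874 = 50.6% if none are. Within these inputs, only the last shows worsening.

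**Range.** In general, share = s(1−f)(1−r) / [(1−f)(1−r) + rc]. With c = 0 this equals s for any f and r, so the benefit disappears from the share. With r = 20%, the shares for all, half and none called in are 0.384/0.968 = 39.7%, 0.384/0.868 = 44.2% and 50.0%. With s = 0.3 and r = 10% they are 0.2592/0.964 = 26.9%, 0.2592/0.914 = 28.4% and 30.0%.

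**Opposite direction.** A second set of assumed inputs lets attendance differ by severity. Per 1000 overdoses: 40 deaths, 300 severe survivors (90% attended = 270) and 660 mild survivors (50% attended = 330). Share = 270/600 = 45.0%. With no clinical effect, if attendance of mild cases rises to 70% (462), the share becomes 270/732 = 36.9%. The attended-severe-or-death count stays at 270 + 40 = 310.

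**The case against.** The strongest objections are these.

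- **No summary measure is stated.** As a count, severe attended survivors fall from 480 to 432 (−10%) in all three main cases, and a condensed article may leave the choice of summary to the full plan. This stands in part: antidote and transport could be analysed as counts. But reaction level, respiratory rate and heart rate are patient-level values, naturally summarised within a group, and the article itself fixes that group as attended survivors. Even as a count, 10 averted deaths arriving severe weaken the fall to 442/480 − 1 = −7.9%.
- **Deaths and attended incidence are already outcomes.** In the no-call-out case, attended overdoses fall from 1000 to 900 (taking deaths as attended), so something shows. But incidence carries no severity information. If all reversed cases are called in, it stays at 1000 while severe-or-fatal cases fall by 10%.
- **The survival part is small.** At 4% fatality, 10 averted deaths are 10/874 = 1.1% of attended survivors. This stands; most of the problem comes from calling.
- **County rates still depend on attendance.** This also stands and is stated under the fix.

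A reader might infer that the restriction always biases towards no benefit or apparent harm. The documents do not support that. The barrier reported in Setting predates the programme, nothing says naloxone holders call less often, and the training teaches calling, which could produce the spurious improvement shown above.

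**Conclusion.** The problem is real and lies in the outcome definitions as written. Five of six general-population secondary outcomes condition on survival and ambulance attendance, both of which the programme can alter, so their before/after contrasts are confounded with case mix in an unknown direction. In the illustration, the same true 10% reduction reads as anything from a fall to 44.8% to no change at 50.0%. It reads as slight worsening (about 50.6%) only if no reversed case is called in and a quarter of would-be deaths arrive as severe survivors.

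These sizes rest on the assumed severe share, reversal rate and call-out; only the fatality range comes from the article. Because the ambulance baseline starts in early 2017, there is at most about one pre-programme year within 2013–2017 in which to see drift in who is attended.

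A reader might also infer that the main conclusion is at risk. It is not: the primary outcome counts opioid deaths in the whole county population and is free of this selection. The five outcomes are secondary and unpowered. The change is worth making before analysis.

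**What to change.** For the effect analysis, express these outcomes as county rates per 100,000 person-years over all attended overdoses, fatal included, in the Poisson model already planned. Examples are attended overdose with RLS-85 at or above a pre-set grade, attended overdose with crew antidote given, and attended overdose with transport. Report alongside them opioid deaths, the combined rate of severe attended overdose or death, and total attended cases. Keep the survivor-only distributions of RLS-85, respiratory rate and heart rate as description.

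The data are already planned: Measures says the ambulance system identifies fatal and non-fatal cases with vital status, and deaths come from national registers. The cost is rewording, a severity cut-off fixed in advance, a rule that counts an attended case that dies only once, and some programming.

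The plan should state the remaining limits. The rates still depend on call-out for severe cases: more calling would hide benefit and less would give false benefit. In the second set of inputs, with no clinical effect, a drop in attendance of severe cases from 90% to 80% takes severe attended overdose or death from 270 + 40 = 310 to 240 + 40 = 280 (−9.7%). Antidote and transport rates would also rise if extra mild calls led to antidote or transport. The combined rate gives no credit when a death becomes a severe survivor, which is why deaths should also be shown separately.
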